### Eligibility criteria for participant clusters

As expertise is generally accepted to be context dependent (Alderson, 2010, Benner et al., 1996, Edwards and Jones, 2007, Eraut, 2006b, Jensen et al., 2007b, Resnik, 2007), all qualified physiotherapy staff from the Cardiff and Vale University Health Board whose majority of time (i.e. greater than 50%) is practised inside the musculoskeletal outpatient context will be eligible to participate in this study. There are two main exclusion criteria, namely members of staff who have already undertaken postgraduate placements as part of Master's education and so would have received similar clinical reasoning facilitation, and rotational staff due to the fact that they will not be present in the department for long enough for both interventions and long term follow up. Currently, the maximum potential number of participating therapists would be 18. It is envisaged that 12 physiotherapists would realistically be recruited and organized into 3 clusters of physiotherapy staff (clustering by site).

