### Objectives

It is the objective of the quantitative component of this study to

1. explore whether facilitation of clinical reasoning skills via a clinical mentoring programme delivered to clusters of physiotherapists (outpatient musculoskeletal physiotherapy departments) yields greater improvements in patient outcomes (measured by risk-adjusted patient outcomes measures from clusters of patients at each step) than those yielded with usual training
2. explore whether facilitation of clinical reasoning skills via a clinical mentoring programme relates to improved physiotherapist performance in clinical reasoning, and whether changes in performance correlate with improvements in patient outcomes

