### Hypotheses

H: There will be a significant difference in the risk-adjusted outcomes of patients whose physiotherapists have received training in clinical reasoning skills via a clinical mentoring programme when compared with those whose physiotherapists have received standard training.

H: There will be no difference in the risk-adjusted outcomes of patients whose physiotherapists have received training in clinical reasoning skills via a clinical mentoring programme and those whose physiotherapists have received standard training.

H: There will be a significant improvement in the performance of physiotherapists who have received training in clinical reasoning skills via a clinical mentoring programme when compared with their performance having received standard training.

H: There will be no improvement in the performance of physiotherapists who have received training in clinical reasoning skills via a clinical mentoring programme when compared with their performance having received standard training.

H: There will be a correlation between improvements in the performance of physiotherapists who have received training in clinical reasoning skills via a clinical mentoring programme and improvements in the clinical outcomes of their patients.

H: There will be no correlation between improvements in the performance of physiotherapists who have received training in clinical reasoning skills via a clinical mentoring programme and improvements in the clinical outcomes of their patients.

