In other studies exploring the effect of educational interventions using crossover methodology, (Cook et al., 2007, Murray et al., 1997a) the point is made that assessment needs to be appropriate – specifically comparisons of students using pre and post intervention testing, a design which has been widely accepted and favoured as a method of assessing the efficacy of skills teaching. While the primary outcome measure for this study - patient outcome measurement - appears to be a new venture for educational interventions, the undertaking of pre-and post-exposure assessment using a widely accepted and nationally and internationally recognized method for assessment of clinical performance satisfies this demand.

All of this serves to underpin the assessment of physiotherapist performance in this study by utilising the University of Birmingham construct for the assessment of improvements in performance of physiotherapists, by observing each therapist with one new patient and one returning patient at three data collection points. Assessment of participants at step 1 will give baseline data on performance levels; assessment of participants during step 2 or 3 will ensure that the independent assessor will not know if therapists have received training or not; assessment during step 4 will give post-intervention measures for all participants.

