## Sample size

The primary outcome measure, the PSFS, shows that for any individual patient, the minimal detectable change (90%CI) for an aggregate of 3 or more activities is 2 points; the minimum detectable change (90%CI) for a single activity is 3 points. In this study, we are looking for a mean difference of 1 point greater improvement in PSFS scores of patients whose physiotherapists who have received the intervention compared with the PSFS scores of patients whose physiotherapists have not yet received the training, as well as a greater proportion of patients achieving the level of minimal detectable difference. The following data values were used for the power calculation: mean changes on the PSFS from usual training to the new training of 1 point, and a Standard Deviation within each group of 2. The standard deviation was on the basis of PSFS data collected from an audit of 191 patients who had received treatment at the University Health

Board physiotherapy department, which is a slightly more conservative estimate than standard deviation values of PSFS outcomes from published studies (Hefford et al., 2009, Young et al., 2010, Costa et al., 2009).

A paper published on the design and analysis of stepped wedge designs (Hussey and Hughes, 2007) investigated the statistical characteristics of the stepped wedge design for CRCTs, and through the use of theoretical calculations and simulation the authors outline a procedure for computing power in stepped wedge trials. Using this procedure, a power calculation was carried out by [name], Senior Lecturer in Statistics, Swansea University in discussion with the rest of the research team. The power calculation is summarised below:

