
External threats to validity in this study could occur from the narrow characteristics of participants in the experiment, care must be taken not to generalize to individuals who do not have the characteristics of participants. Therefore, while methods and results may be of interest to - and have relevance for - other allied health professions, additional experiments would need to be performed to ascertain whether similar results are elicited. Likewise, due to the narrow characteristics of the setting of participants in this

experiment (musculo-skeletal outpatients), care must be taken not to generalize to individuals in other settings (inpatient settings) without further experimentation.

Other threats to validity could involve statistical conclusion threats which occur from inadequate statistical power or violation of statistical assumptions leading the researcher to draw inaccurate inferences or conclusions from the data. In addition, construct validity can be threatened when the researcher uses inadequate definitions and measures of variables. The measures of variables have already been outlined as appropriate, for the variables that have been accurately defined, and the research study has been appropriately powered.

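### The blanket claim of adequate power does not extend to the third hypothesis, the therapist-level correlation, which rests on about 12 units and has no power calculation behind it

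*Protocol*

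**What the plan says.** Under *Validity approaches in quantitative methods*, the protocol lists inadequate statistical power among the threats to statistical conclusions. It closes the point with the statement that the measures are appropriate "and the research study has been appropriately powered". The same statement is repeated under *Validity, Credibility & Trustworthiness*, in the quantitative subsection. Neither place limits it to a particular outcome or hypothesis.

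*Hypotheses* contains three H1/H0 pairs in the same form. The third reads "There will be a correlation between improvements in the performance of physiotherapists who have received training in clinical reasoning skills", continuing to improvements in the clinical outcomes of their patients. The matching part of the second objective is to explore the effect on performance "and whether changes in performance correlate with improvements in patient outcomes".

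*Sample size* and Appendix E size one comparison only. The effect is "mean changes on the PSFS from usual training to the new training of 1 point", with a within-group SD of 2, 12 physiotherapists, 4 time points and 9 patients per physiotherapist per time point. The stated power is 0.805. No power, expected correlation or precision is given for the third hypothesis.

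On numbers of therapists, *Eligibility criteria for participant clusters* says "It is envisaged that 12 physiotherapists would realistically be recruited", and that "the maximum potential number of participating therapists would be 18". Performance is scored "by observing each therapist with one new patient and one returning patient at three data collection points" (*Therapist Outcome Measures*).

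**The concern.** A power calculation supports the hypothesis it was made for. The one here concerns a mean difference over 432 patient observations, and its model has no parameter describing how one therapist's gain relates to another quantity. The third hypothesis is about therapists, and there are about a dozen of them however many patients each one treats.

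The hypothesis matters to the argument of the study. The purpose statement sets out to test the theory that developing clinical reasoning improves patient outcomes, and the literature review describes trials in which clinicians changed but patients did not. A non-significant correlation would therefore be easy to read as a substantive finding. With an unqualified assurance of adequate power in the protocol, nothing would warn the reader against retaining the null as if it had been fairly tested.

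**Working it through.** **1. The protocol's own figure.** Inputs from *Power calculation: summary* and Appendix E: I = 12, T = 4, N = 9, σₑ² = 4, τ² = 1, so σ² = 4/9 = 0.4444; U = 24, W = 224, V = 56.

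Var(θ̂) = Iσ²(σ² + Tτ²) / [(IU − W)σ² + (U² + ITU − TW − IV)τ²]

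- Numerator: 5.3333 × 4.4444 = 23.704
- Denominator: 64 × 0.4444 + (576 + 1152 − 896 − 672) × 1 = 28.444 + 160 = 188.444
- Var = 0.125786, SD = 0.35466, Δ = 1/0.35466 = 2.8196
- Power = 1 + Φ(−1.96 − 2.8196) − Φ(1.96 − 2.8196) = 0.805

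The figure reproduces, for the mean PSFS difference.

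**2. Correlation with no measurement error.** Take one pair of gains per therapist and a two-sided 5% t test of a Pearson correlation. At n = 12, t(0.975; 10) = 2.228, so the critical |r| = 2.228/√(10 + 2.228²) = 0.576. Power by bivariate-normal simulation (200,000 runs):

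| True r | n = 12 | n = 18 |
|---|---|---|
| 0.3 | 0.16 | 0.23 |
| 0.5 | 0.40 | 0.59 |
| 0.6 | 0.58 | 0.79 |
| 0.7 | 0.78 | 0.93 |
| 0.8 | 0.93 | 0.99 |

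By Fisher's z, 80% power at r = 0.5 needs ((1.96 + 0.84)/atanh 0.5)² + 3, about 30 therapists.

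**3. Sampling error in the PSFS gain.** A therapist's gain is a difference between means of small groups of patients. With σₑ² = 4 and 9 patients per step:

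- one step against one step: 4/9 + 4/9 = 0.89
- two steps against two: 4/18 + 4/18 = 0.44

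If the true gains have SD s, reliability is s²/(s² + error variance), and the correlation is multiplied by its square root. The protocol does not give s; values of 0.5 and 1.0 points are assumed. Power at n = 12:

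| Error variance | s | Reliability | True r = 0.5 | True r = 0.7 | True r = 0.8 |
|---|---|---|---|---|---|
| 0.89 | 0.5 | 0.22 | 0.11 | 0.18 | 0.23 |
| 0.44 | 0.5 | 0.36 | 0.16 | 0.28 | 0.37 |
| 0.89 | 1.0 | 0.53 | 0.22 | 0.42 | 0.55 |
| 0.44 | 1.0 | 0.69 | 0.28 | 0.55 | 0.71 |

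Two features are not modelled, and both would probably lower these figures: error in a performance score based on one new and one returning patient, and the grouping of the therapists into three site pairs.

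**4. What a null result would say.** For an observed r = 0 and n = 12, the 95% interval is tanh(±1.96/√9) = tanh(±0.653), or about −0.57 to 0.57.

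**The case against.** The strongest reply is that the statement should be read in context. The protocol names a single primary outcome because of multiple testing and ties the sample size to it, so a claim of adequate power would ordinarily mean power for that outcome. Not powering a secondary aim is normal practice. The mixed-methods section also treats performance and outcomes as material to be compared case by case, which is exploratory in spirit.

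Much of this stands, and it is why the point is small. It does not remove it. The claim is made twice without a limit, as the answer to a named threat. The verb *explore* does not mark the correlation as exploratory, because the first objective, the primary comparison, uses the same verb. In *Hypotheses* the correlation has the same formal status as the primary.

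The reply is also right that the protocol fixes neither a correlation method nor a unit of analysis, and that the third hypothesis refers to clinical outcomes generally. PSFS is the natural reading but not the only one. A reader might infer that the protocol plans to correlate 12 raw gain scores, or to treat a non-significant result as proof of no link. It says neither. The figures above show what 12 therapists can support under a simple analysis; they do not criticise a stated method. A repeated-measures analysis could use more scores per therapist, but it would not add therapists.

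**Conclusion.** The statement of adequate power holds for the mean PSFS difference (0.805) and is unsupported for the third hypothesis. For a moderate true correlation of 0.5, power with 12 therapists is about 0.40 before measurement error. It is about 0.11 to 0.28 after sampling error in the PSFS change, for an assumed SD of true gains of 0.5 to 1.0 points. Over the same range, it reaches at most about 0.71 at a true correlation of 0.8. A null result would leave correlations up to about 0.57 in either direction open.

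These are ranges under assumptions, since the protocol states neither the true correlation nor the spread of true gains. It would be wrong to take 0.40 as a ceiling: without measurement error, power is 0.78 at r = 0.7 with 12 therapists, and 0.59 at r = 0.5 if all 18 take part. It would also be wrong to infer that the trial as a whole is underpowered, because this check does not challenge the primary calculation. Severity: minor.

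**What to change.** In both validity sections, limit the statement to the primary comparison of mean PSFS change. In *Hypotheses*, label the third pair exploratory. State that the therapist-level association will be reported as an estimate with its confidence interval, and that a non-significant result is not evidence of no link.

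A patient-level model with therapist performance as a covariate is an option, not a requirement. It would allow for sampling error in the patient outcomes. It would not add therapists or remove error in the performance score, and performance is scored at only three of the four steps, so one step per therapist would lack a score.

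The required changes are wording only and need no new data. The cost is that the third hypothesis can no longer be claimed as confirmed or refuted.

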## **Conclusions and applications**

To conclude the discussion of all of these issues, the selection of the stepped-wedge design would appear to be the most appropriate to address the research problem and research questions. The alternatives of parallel designs (crossover or non-crossover) would be limited by issues relating to balancing covariates, sample size, logistics of intervention delivery and potential contamination. The arguments presented for the advantages of crossover methodology used elsewhere in healthcare education are compelling, and the use of stepped-wedge designs in evaluating educational interventions reinforce these arguments. By employing a longitudinal study design, improvements are expected to be made over time as skills are learned, applied and refined; the stepped-wedge design allows for the investigation of time as a variable in the final analysis. The timings of data collection are important; early implementation of the intervention within the time period, data collection near the end of the time period, and sufficiently long time periods to allow for delays in effects from the intensive mentoring for clinical reasoning facilitation, due to time required to consolidate and make practice changes. The use of usual training as control is also appropriate; a non intervention control in this instance would be ethically unacceptable – withdrawing training for staff responsible for patient care - as well as unhelpful for cost-effectiveness analysis where comparison should be made as closely as possible with usual practice (Gray et al., 2010). The assessment issue of recognized assessment tools pre- and post-exposure raised by Murray and colleagues (Murray et al., 1997a) is also addressed.

The overall structure of the quantitative component of the project is outlined and summarized in the consort diagram in figure 5.

Figure 5: CONSORT 2010 Flow Diagram of Quantitative Component of Trial

[figure not shown]

## Qualitative Component

Cresswell (2009) outlines characteristics of qualitative research, many of which lend themselves to the clinical context of this study. Qualitative research tends to involve data collection in the natural setting – that is, in the field, at the site where participants experience the issue or problem under study; in this case, in the clinical context of the participants, with the researcher as key instrument collecting multiple sources of data. This allows for collaboration with the participants interactively during the data analysis, so that the participants have a chance to shape the themes or abstractions that emerge from the process, thus allowing the researcher to keep a focus on learning the meaning that the participants hold about the problem or issue, not the meaning that the researcher brings to the research. Qualitative data from mentors and participating therapists will allow for a more holistic approach to what has been identified as a complex issue under study (Kalet et al., 2010). In reporting multiple perspectives, it is hoped that the many factors involved in the process of facilitating clinical reasoning in order to achieve improved clinical outcomes will be identified, allowing for a broader discussion on the picture that emerges.

### Type and definition of design used

Creswell (2009) outlines four main categories of qualitative data collection procedures: collecting information through unstructured or semi structured observations and interviews, documents, and audio-visual materials. Semi-structured interviews and observations will be used for this study, which will be defined and reasons for their selection will be outlined below.

#### Semi-structured interviews

Murphy et al (Murphy et al., 1998) identify the use of interviews in scenarios where researchers seek to discover what people think about the world they live in, how they evaluate their experiences within it and why they behave as they do, interpreting the choice to use interviews to collect data as, “If you want to understand what people do, believe and think, ask them” (p112 Murphy et al., 1998). Qualitative interviews allow relatively rapid data collection based on what interviewees say about their beliefs and attitudes, action and behaviour (Pope and Mays, 2006). Miles and Huberman (1984), Noaks and Wincup (2004) and Silverman (2010) strongly suggest that researchers do not present their main research question directly to the respondents themselves on the basis that this can affect their responses, and can lead to simply reporting back what respondents have told you instead of undertaking and reporting careful data analysis. Bearing this in mind, the general aim of the interviews in this study is to encourage the participants to speak personally and at length about their professional development as physiotherapists, while at the same time covering the issues which are of interest in answering the research questions – namely, to explore the participants’ and mentors’ experiences about the interventions in the study - mentoring and training, and their evaluation of both. As a result, there will need to be a balance maintained between what is interesting to the researcher and what is interesting to the participant (Silverman, 2006). To meet this aim, face-to-face interviews with participants and mentors will be conducted at the end of the intervention period. The closeness of the lead researcher to the clinic sites will allow for this rather than needing to interview participants by telephone. The subsequent questions that arise are what type of interview to employ and whether to perform interviews individually or to utilize focus groups to gain these reports from participants?

Several authors have sought to discuss the distinction and differences between structured and unstructured interviews (Burgess, 1982b; Habermann-Little, 1991; Fontana and Frey, 1994). However, some authors (Murphy et al., 1998, Britten, 2006) challenge the term ‘unstructured’ as misleading due to the impossibility of conceiving an interview which is totally without structure, and acknowledging that without structure

there would be no guarantee that data collection would be relevant to the research question. Instead they concur with Richardson and colleagues (Richardson et al., 1965) to suggest that it is more accurate to consider interviews as ranged across continuum of standardization. Britten (Britten, 2006) divides interviews into structured, semi-structured and depth. This division describes structured interviews as being performed by interviewers administering questionnaires and asking questions in a standardized manner; semi-structured interviews using open-ended questions based on a loose structure which defines the area to be explored, but which allows deviation to further explore responses and ideas; depth interviews are less structured again, with questions based on what the interviewee says, and only one or two issues explored in greater depth. This study will use semi-structured interviews, with structured interviews being too rigid and imposing to meet the aims of the exploratory nature of this element of the research in discovering the interviewees' own perspectives and frameworks of meaning (Britten, 2006) and depth interviews lacking the necessary breadth to explore the issues identified from previous qualitative research (Jensen et al., 2007b, Resnik, 2007).

Kitzinger (Kitzinger, 1995, Kitzinger, 2006) suggests the use of focus groups for studying cultural values such as work place cultures – such as the training culture in the health board under study in this research. She suggests this on the basis that focus group interviews tap into interpersonal communication to highlight cultural values or group norms. While Morgan (Morgan, 2010) also acknowledges such strengths, he also highlights the difficulties and challenges of such group dynamics; for example the voicing of group norms may silence individual objections and voices of dissent, and also the fact that other research participants are present means that the confidentiality of the research is compromised. This is of particular concern in the context of this research where great care is being taken to ensure that individual therapists' confidentiality is safeguarded both for their outcomes and their interview data. For example, therapists will be encouraged to discuss their relationship with their mentor; this is potentially sensitive data requiring absolute confidentiality.

There is a pragmatic argument for using focus group interviews over individual interviews. Citing one of the few studies that compare output of individual interviews and focus group interviews (in the generation of ideas) by Fern (Fern, 1982), - which showed that focus groups produced fewer, lower quality ideas when compared with individual interviews- Morgan (Morgan, 1996) concedes that it does not support the notion that focus groups have a synergy leading to greater depth and breadth of data, but suggests that focus groups could be selected due to their efficiency of output – the same number of ideas from Fern's results being produced from two focus groups as in 10 individual interviews. While - in this study - focus group interviews would allow for collection of this data at fewer visits, the staggered start and finish times of participants in the process as dictated by the crossover design would mean long time delays for some participants before interview, making recall more challenging.

For these methodological and pragmatic reasons, individual interviews rather than focus groups will be used. The interviews will aim to elicit the views and opinions from the participants and their mentors on the research problem, the intervention, and their own reflections on the whole process.

